### **12.1. Population for analysis**

#### **A. Intention-to-treat population (ITT)**

##### **A.1. Population for the main analysis**

This population includes all subjects in the control group that were included in the study and all subjects in the experimental group who have taken at least one dose of Kaletra ®. This analysis will provide estimates of treatment effect that will reflect the usual practice with greater accuracy.

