### **Baseline visit:**

If laboratory data for confirming screening criteria have been obtained within two months of study recruitment and are available, the screening visit may be the same as the baseline visit.

The study drugs should start to be taken within 24 hours of the baseline visit. The following assessments should be available at the baseline visit:

- Physical examination (vital signs, height and weight).
- Quality of life questionnaires (MOS-HIV and EQ-5D)
- A negative urine pregnancy test for women of childbearing age.

- Complete blood count (red blood cell count, white blood cell count and differential, and platelet count).
- Fasting chemistry profile (alkaline phosphatase, ALT, AST, GGT, total bilirubin, creatinine, glucose, potassium, sodium, uric acid, lipid profile (total cholesterol, HDL-C, LDL-C, VLDL-C, triglycerides).
- CD4 cell count
- HIV-1 RNA in plasma: This will be measured in real time at the site using the standard virological methods at each site. The same methods should be used throughout the study for each subject.
- CESTA questionnaire to assess satisfaction with antiretroviral treatment.
- GEEMA questionnaire to assess treatment adherence
- VAS to assess treatment adherence
- Recording of concomitant medication
- Adverse events

Once the baseline visit procedures and assessments are reviewed, subjects will be centrally randomized at the study data center after data are received.

Patients randomized to group B will return for HIV RNA monitoring at treatment week 4 (+/- 2 days)

The following assessments should be completed at the **week 12 and week 24 visits or at the study discontinuation visit**. Study visits should be scheduled to occur within  $\pm 1$  week of the date specified for weeks 12 and 24, calculating the dates from the baseline visit:

- Physical examination (vital signs, weight).
- Complete blood count (red blood cell count, white blood cell count and differential, and platelet count)
- Fasting chemistry profile (alkaline phosphatase, ALT, AST, GGT, total bilirubin, creatinine, glucose, potassium, sodium, uric acid, lipid profile (total cholesterol, HDL-C, LDL-C, VLDL-C, triglycerides)
- CD4 cell count
- HIV-1 RNA in plasma: If the patient shows at any time a detectable viral load (> 50 copies/mL), the test should be repeated within 2 weeks for confirmation. Annex 1 provides suggestions for management of these cases
- Concomitant medication
- Adverse events

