#### **Statistical analysis**

Baseline characteristics of study groups will be compared using an analysis of variance (ANOVA). The mean, median, standard deviation, and range will be provided for continuous variables, and the distribution of absolute frequencies and percentages will be given for discrete variables. When required, 95% confidence intervals will be calculated. Discrete variables will be compared using a Chi-square test.

For quality of life analysis, the primary population will include all patients with data available from baseline up to at least one post-baseline visit (e.g. the intention-to-treat population).

In case of patient abandonment is taken as a post-treatment evaluation the one obtained at the time of abandonment. If there is no post-treatment evaluation as a neutral value, baseline observation value will be carried forward until month 24 or the time of abandonment (Baseline Observation Carried Forward).

The main deadline to study results will be week 24 of the study. An analysis of covariance (ANCOVA) will be used for quality of life comparison. The model will include the baseline values for the items in the MOS-HIV questionnaire, age and sex as covariates, in the control and study groups. For primary endpoint analysis, the values in the MOS-HIV and EQ-5D questionnaires in the different weeks as compared to baseline will be provided for each treatment group.

An analysis of covariance (ANCOVA) will be used for comparisons between both treatment groups.

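### The primary analysis set is fixed in two incompatible ways under the name ITT, one with a first-dose condition on the experimental arm only, and neither is all randomised patients.

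*Protocol*

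**What the plan says.** Section 12.1, under the ITT heading and the subheading "Population for the main analysis", gives each arm its own rule. The set is made up of "all subjects in the control group that were included in the study and all subjects in the experimental group who have taken at least" a single Kaletra dose. Controls thus enter on inclusion alone, and experimental patients only on treatment. Set A.2 is A.1 minus certain withdrawals. A separate safety set is based on receipt of study drug.

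Section 12.4 (Statistical analysis) states a second rule for quality of life, the primary endpoint: "the primary population will include all patients with data available from baseline up to at least one post-baseline visit". It ties this to the same name: "e.g. the intention-to-treat population". The next paragraph uses the assessment made at withdrawal where there is one, and otherwise says: "If there is no post-treatment evaluation as a neutral value, baseline observation value will be carried forward until month 24" or withdrawal. (Follow-up ends at week 24, so month is presumably a slip for week.)

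On timing, section 8.2.3 says: "The study drugs should start to be taken within 24 hours of the baseline visit". Central randomisation follows review of that visit, and section 5.3 has the investigator learn the arm by telephone. In the section 8.2.1 schedule, MOS-HIV and EQ-5D are collected at baseline, week 24 and early discontinuation. The week 4 visit is for the experimental arm only.

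**The concern.** An intention-to-treat comparison is protected because membership of the set is settled at randomisation. Here A.1 lets an event after an unblinded allocation decide membership, and only in the arm asked to change treatment. A patient allocated to the switch who then declines it leaves the set. The equivalent control simply carries on with current therapy and stays in.

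The second difficulty is that sections 12.1 and 12.4 cannot both be followed. A statistical analysis plan must contradict one of them, so the choice of primary set could stay open until shortly before database lock in an open-label trial. At stake is which patients the headline quality-of-life difference describes, and whether the two groups compared are still the randomised groups.

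**Working it through.** **The two definitions side by side**

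- Control with no post-baseline data: in under 12.1 A.1, out under 12.4.
- Experimental patient never dosed but seen after baseline: out under A.1, in under 12.4.
- Experimental patient never dosed and not seen again: out under both.

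So neither set contains the other, and neither is all randomised patients. A.1 also does not say that a control being included means being randomised.

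**What counts as post-baseline data in 12.4.** The text does not say, and each reading has a problem.

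- If it means quality-of-life data, patients with no post-treatment evaluation are already out, and the carry-forward rule has nobody to act on.
- If any visit counts, a patient seen at week 12 and then lost without a questionnaire stays in, and the rule works. But experimental patients can qualify at week 4 and controls have no such visit, so entry is unequal between arms.

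**Inputs (Sample size and rationale):** control mean 61.84, experimental mean 68.02, SD 20, 1:2 allocation, two-sided alpha 0.05, power 80%, 7% loss, 130 + 260 = 390 patients.

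**Plan's own figure.** Difference = 68.02 - 61.84 = 6.18. Controls needed = (1 + 1/2) x (1.960 + 0.842)² x 20² / 6.18² = 123.3, rounded up to 124. With 248 experimental patients the total is 372, as stated, and power is 80.2%.

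**Full randomised set.** SE = 20 x sqrt(1/130 + 1/260) = 2.15 points. Power at 6.18 points is 82.0%.

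**Keeping or excluding patients without post-baseline data (ceiling).** 0.07 x 390 = 27.3, so at most 27 patients, if every loss lacks all post-baseline data.

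- Kept with baseline carried forward (no change): 0.93 x 6.18 = 5.75 points, power 76.3%.
- Excluded: 6.18 points, power 79.2%.
- Gap: 6.18 - 5.75 = 0.43 points, or 0.43 / 2.15 = 0.20 SE.

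**One-sided dose condition.** The protocol gives no never-started fraction f, so it is assumed. If never-starters do not change, the as-randomised effect is 6.18 x (1 - f), and excluding them adds 6.18 x f:

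| f (assumed) | Patients of 260 | As-randomised effect | Power | Added by exclusion |
|---|---|---|---|---|
| 2% | 5.2 | 6.06 | 80.5% | 0.12 (0.06 SE) |
| 5% | 13 | 5.87 | 78.0% | 0.31 (0.14 SE) |

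**No true treatment difference.** If never-starters score g points worse at week 24 than the rest of their arm, dropping them shifts the experimental mean by f x g. Both f and g are assumed:

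| f | g | Shift | Two-sided type I error |
|---|---|---|---|
| 2% | 10 | 0.2 | 5.1% |
| 5% | 10 | 0.5 | 5.6% |
| 5% | 20 | 1.0 | 7.5% |
| 7% | 20 | 1.4 | 9.9% |

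With g = 0 there is no shift.

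**The case against.** The best defence is that little is at stake numerically. Drug is due within 24 hours of the baseline visit, so never-starters may be very few. Even the ceiling gap is a fifth of a standard error. The protocol also defers detail to a statistical analysis plan. The point about size stands. The deferral does not help, because the protocol itself fixes the primary set, twice, under one name.

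Three stronger readings are tempting, and the documents do not support them.

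- A reader might infer that the section 12.4 set is close to a completers set. Questionnaires are also due at the early-discontinuation visit (sections 8.2.1, 8.2.3 and 8.2.5), and 12.4 uses the value obtained at withdrawal, so patients who stop and attend that visit stay in. Patients completing 24 weeks form the separate per-protocol set.
- A reader might infer that the carry-forward rule flatly contradicts the population definition. It does so only if post-baseline data means quality-of-life data.
- A reader might infer that A.1 necessarily favours the experimental arm. If never-starters merely fail to change, dropping them undoes dilution of a real effect and leaves a null comparison unbiased. Inflated type I error needs them to differ from the rest. The 9.9% figure takes a 7% never-started fraction and a deficit of one full SD, neither from the protocol.

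**Conclusion.** The point holds as a defect of definition. The main set applies a post-randomisation condition to one arm of an open-label trial. A second, incompatible rule carries the same name. The protocol offers no all-randomised alternative. This is wrong as written whatever the eventual numbers, because the primary analysis cannot be carried out consistently with both sections.

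The likely effect is small and cannot be pinned down from the protocol. The 0.43-point gap, 7% of the design effect, is an upper limit under the planned loss: it needs every lost patient to lack post-baseline data and to be given no change. The 0.12-0.31 points from the dose condition rest on an assumed 2-5% never starting. Direction under the null depends on how never-starters compare with the rest, on which the protocol is silent. The case for changing the text is therefore the integrity of the randomised comparison and a single executable definition, not a demonstrated large bias.

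**What to change.** State one primary set, in the same words, in sections 12.1 and 12.4: all randomised patients, analysed in the arm assigned, regardless of dosing or post-baseline data.

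- Delete the first-dose condition from A.1 and the post-baseline condition from 12.4.
- Keep the stated rule for missing week-24 values and say that it applies to this set.
- Note that A.2 is built on A.1 and changes with it.
- Leave the dose-based definition to the safety population.

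The cost is a few sentences in section 12, a slightly smaller expected effect and somewhat lower power. At the 7% ceiling with baseline carried forward, power is about 76%, against about 79% if those patients were excluded and 80% planned. Part of that is not new: A.1 already keeps controls and dosed experimental patients who have no follow-up data.

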##### **A.2. Population for the secondary analysis**

This population includes all subjects covered in "A.1.", but excluding those patients who have left the study for adverse events (suffer diarrhea). This analysis will assess the likely increase in difference in quality of life that is believed to provide a higher level of neglect in the experimental group because of an expected adverse event, which will give more optimistic estimates of the difference between treatments

#### **B. Per protocol population (PP):**

This population will include all patients who complete the 24 weeks of follow-up.

#### **C. Safety population:**

This population will include all subjects who have received at least one dose of study drug.

### **12.2. Primary endpoint**

- To compare the quality of life from baseline to 24 weeks in patients who start monotherapy with LPV/r tablets versus patients on triple therapy containing any boosted protease inhibitor (PI) using the Medical Outcomes Study HIV Health Survey (MOS-HIV) and the visual analog scale EuroQol 5D (EQ-5D).

### **12.3. Secondary endpoints**

- Assessment of treatment satisfaction of HIV+ patients who start monotherapy with LPV/r tablets versus triple therapy containing any PI using the CESTA questionnaire (Spanish Questionnaire of Satisfaction with Antiretroviral Treatment) from the baseline visit to study week 24.

- Assessment of treatment adherence by HIV+ patients who start monotherapy with LPV/r tablets versus triple therapy containing any PI using the GEEMA questionnaires and a visual analog scale (VAS).
- Assessment of regimen tolerability and safety in HIV+ patients who start monotherapy with LPV/r tablets versus triple therapy containing any PI.
- Proportion of patients with a viral load <50 copies/mL of HIV RNA at 24 weeks in HIV+ patients who start monotherapy with LPV/r tablets versus triple therapy containing any PI. A viral load >500 copies/mL of viral RNA (HIV-1) confirmed at study week 24 will be considered as virological failure.
- Changes in immune response in HIV+ patients who start monotherapy with LPV/r tablets versus triple therapy containing any PI, as measured through the change in CD4+ cell count from the baseline visit to study week 24

#### **12.4. Statistical methods.**

The statistical tests to be used and the specific study of each variable included will be described in detail in the Statistical Analysis Plan that will be prepared before the database is locked. However, a brief description is given below.

All analyses will be performed using statistical software SPSS, version 15.0 or higher. All statistical tests will be two-sided, with a significance level of 0.05.

#### **Statistical analysis**

Baseline characteristics of study groups will be compared using an analysis of variance (ANOVA). The mean, median, standard deviation, and range will be provided for continuous variables, and the distribution of absolute frequencies and percentages will be given for discrete variables. When required, 95% confidence intervals will be calculated. Discrete variables will be compared using a Chi-square test.

For quality of life analysis, the primary population will include all patients with data available from baseline up to at least one post-baseline visit (e.g. the intention-to-treat population).

In case of patient abandonment is taken as a post-treatment evaluation the one obtained at the time of abandonment. If there is no post-treatment evaluation as a neutral value, baseline observation value will be carried forward until month 24 or the time of abandonment (Baseline Observation Carried Forward).

The main deadline to study results will be week 24 of the study. An analysis of covariance (ANCOVA) will be used for quality of life comparison. The model will include the baseline values for the items in the MOS-HIV questionnaire, age and sex as covariates, in the control and study groups. For primary endpoint analysis, the values in the MOS-HIV and EQ-5D questionnaires in the different weeks as compared to baseline will be provided for each treatment group.

An analysis of covariance (ANCOVA) will be used for comparisons between both treatment groups.

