### **5.3 PATIENT RANDOMIZATION**

Randomization will be centralized and will be performed from the study data center upon data reception. Central randomization will be performed.

Before patients begin the study, patients will be randomized according to a randomization list. The list will be created by generating pseudo-random numbers of Wichmann and Hill (1982) and modified by McLeod (1985). The size of the blocks will be 4 to try to balance the treatment arms of the total sample and within each center. No stratification was planned by any other factor

The randomization list will be centralized and hidden from the investigators. Investigators will access the allocated treatment by telephone at the time of randomization with the sponsor or who is assigned on its behalf. CRD corresponding page will be sent by fax prior to the phone call. CRD corresponding page confirms that the patient meets all inclusion criteria and none of exclusion in order to know the branch of study is given and the number of patients used for

the same. This information is written back to the researcher in the same format for receiving your application, including the number assigned to the patient and the branch of study.

Patients will be randomized in a 1:2 ratio to one of the following two options:

**Control group (A):** Patients will continue on antiretroviral triple therapy based on any PI boosted with ritonavir.

**Experimental group (B):** Patients will be switched from antiretroviral triple therapy based on any PI boosted with ritonavir to LPV/r monotherapy (co-formulated tablets).

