### ***Sample size and rationale***

In a similar study population (e.g. HIV+ patients with an undetectable viral load, i.e. < 50 copies/mL of HIV-1 RNA), the mean baseline quality of life score measured with the MOS-HIV questionnaire was 61.84 [24]. As standard deviation is not available, we assume for all calculations that standard deviation will be the highest score minus the lowest score in the quality of life dimension (e.g. 100) divided by 5, which gives 20. This standard deviation of 20 is the same as found in HIV-infected asymptomatic patients, patients with AIDS-related symptoms, or patients with AIDS and a CD4 cell count <100 [25]. Assuming, then, that quality of life will remain unchanged in patients assigned to the control group (maintaining current antiretroviral therapy) and will improve by 10% (e.g. to scores of 68.02) in patients assigned to the experimental group (LPV/r® as monotherapy), with a 1:2 ratio, an 80% statistical power, and a two-sided alpha of 0.05, 372 patients would be required, 248 randomized to the experimental group and 124 randomized to continue on the current antiretroviral therapy.

Assuming 7% follow-up losses, the final sample size required will be of 260 patients for the experimental group and 130 patients for the control group, i.e. a total of 390 patients.

Because the triple antiretroviral therapy based on a PI boosted with ritonavir (control treatment) has been widely studied for a practical sense, it has been considered to allocate the sample to twice the experimental treatment (1:2, respectively) [24 ], [26].

This distribution of the sample (1:2) compared with the distribution of equal groups (1:1) ensures greater security in the contrast of the study to a possible greater variability of response in the quality of life in the experimental group since this group is expected to more patients with diarrhea to begin new therapy. [27]

Also it will provide an improved accuracy in estimating mean and smaller confidence intervals, for example, more than 1% in the estimated proportions near 50%.

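### The stated quality-of-life ANCOVA names baseline MOS-HIV items rather than the baseline of each score analysed and leaves out centre, which costs precision and is mildly conservative

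*Protocol*

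**What the plan says.** Under *Statistical analysis* in section 12.4, the protocol says that ANCOVA will compare quality of life at week 24 and gives one covariate list: "The model will include the baseline values for the items in the MOS-HIV questionnaire, age and sex as covariates". A later sentence names ANCOVA again for comparing the two groups and lists no covariates. No sentence names a baseline EQ-5D value or centre.

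Sections 8.1.1 and 12.2 define the primary endpoint on two instruments, MOS-HIV and the EQ-5D visual analogue scale, as change from baseline to week 24. Section 5.3 uses blocks of 4 "to try to balance the treatment arms of the total sample and within each center" and says that no other stratification factor was planned. The sample-size section defends 1:2 allocation partly by pointing "to a possible greater variability of response in the quality of life in the experimental group".

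Section 12.4 opens by calling itself a brief description and leaves the handling of each variable to a statistical analysis plan, to be written before database lock.

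**The concern.** In an ANCOVA of a patient-reported score, the covariate that does most of the work is the baseline value of that same score. The sentence does not name it for either instrument. For MOS-HIV it names items, which taken at face value means many correlated ordinal responses in place of one summary. For EQ-5D VAS it names nothing of that instrument's own. Centre is a factor that the allocation tries to balance. Balancing it makes the treatment estimate more precise if centre predicts outcome, but a model without centre does not see that gain and reports too large a standard error.

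The design rests on "an 80% statistical power, and a two-sided alpha of 0.05" with nothing in reserve, so avoidable loss of precision on the primary measures is worth removing. Because the protocol states a covariate set, an analysis plan that follows it will inherit the weakness.

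**Working it through.** **Inputs from the protocol.** "All statistical tests will be two-sided, with a significance level of 0.05"; power 80%; "the mean baseline quality of life score measured with the MOS-HIV questionnaire was 61.84"; the score "will improve by 10% (e.g. to scores of 68.02) in patients assigned to the experimental group", so the difference is 68.02 − 61.84 = 6.18; SD from the range of 100 "divided by 5, which gives 20"; allocation 1:2.

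**Assumed, because the protocol gives no figure.** Correlation of baseline with week 24 of 0.5–0.7 for the same score and 0.3–0.4 across instruments; intra-centre correlation (ICC) of 0.02–0.10; 31 centres of 12 patients in the simulation.

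**The plan's own sample size.** n_A = (1 + 1/2)(1.960 + 0.842)² × 20² / 6.18² = 123.3, rounded up to 124. Then n_B = 248 and the total is 372, as stated. Power at 124/248 is 80.2%. This calculation takes no credit for any covariate.

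**Items against one score.** Annex 3 holds 3 + 6 + 2 + 1 + 5 + 8 + 4 + 4 + 2 = 35 MOS-HIV responses. With intercept, arm, age and sex, a one-score model has 5 parameters and a 35-item model has 39. If the items carry nothing beyond their total, the standard error grows by about √((372 − 5)/(372 − 39)) = √(367/333) = 1.050. A null simulation (8,000 replicates, SD 20, own-baseline correlation 0.5, age and sex left out, ICC 0) agrees:

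| Model | Mean model SE | Empirical SD | Type I error |
|---|---|---|---|
| no baseline | 2.198 | 2.183 | 0.048 |
| one baseline score | 1.906 | 1.905 | 0.052 |
| 35 items | 2.000 | 1.997 | 0.051 |

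The ratio is 2.000/1.906 = 1.049. The information lost is 1 − (1.906/2.000)² = 0.092, or about 34 of 372 patients. In every row the standard error is valid.

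**EQ-5D VAS without its own baseline.** Adjusting for a covariate with correlation r multiplies the residual SD by √(1 − r²). The power column borrows the MOS-HIV planning figures and is only illustrative for EQ-5D.

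| r | √(1 − r²) | Power at 124/248 |
|---|---|---|
| 0 | 1.000 | 80.2% |
| 0.3 | 0.954 | 83.8% |
| 0.4 | 0.917 | about 87% |
| 0.5 | 0.866 | 90.0% |
| 0.7 | 0.714 | 97.6% |

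The own baseline therefore removes 13–29% of the residual SD at r = 0.5–0.7. MOS-HIV baselines would recover 5–8% at a cross-instrument r of 0.3–0.4. Analysing change instead multiplies the SD by √(2(1 − r)), which is 1.00 at r = 0.5 and 0.77 at r = 0.7. Change alone therefore gains nothing at 0.5 and 23% at 0.7.

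**Centre omitted, arms balanced within centre.** With no covariate, model SE over true SE is 1/√(1 − ICC): 1.010 at ICC 0.02 and 1.054 at 0.10. With an own baseline at r = 0.5 the residual variance is 0.75, and the ratio is √(0.75/(0.75 − ICC)): 1.014 at 0.02, 1.035 at 0.05 and 1.074 at 0.10. The same simulation, one-score model, gives:

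| ICC | Centre in model | Mean model SE | Empirical SD | Type I error |
|---|---|---|---|---|
| 0.05 | no | 1.906 | 1.820 | 0.039 |
| 0.05 | yes | 1.843 | 1.820 | 0.045 |
| 0.10 | no | 1.903 | 1.782 | 0.036 |
| 0.10 | yes | 1.775 | 1.782 | 0.050 |

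At ICC 0 omission does no harm. The simulation assumed exact 1:2 balance within centre. A block of 4 split 1:2 would need 4/3 and 8/3 patients, so section 5.3 cannot deliver that balance exactly, and the true effect is smaller.

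**Unequal variance.** The SDs of 25 and 17 in the experimental group are assumed; the protocol uses 20 throughout. With 130/260 patients and SD 20 in control against 25 in the experimental group, the true SE is √(400/130 + 625/260) = 2.341. The pooled SE is √(550.2 × (1/130 + 1/260)) = 2.520, a ratio of 1.076 and a true alpha of about 3.5%. With SD 17 in the experimental group the ratio is 0.948 and alpha about 6.3%.

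**The case against.** A reader might infer that the primary standard errors are wrong throughout. They are not. Entering items, or lacking an own baseline, leaves them valid, and even the literal 35-item model beats no adjustment (2.000 against 2.198). The trial was sized on the unadjusted SD, so these choices do not push power below plan. Only the omission of centre miscalibrates the standard error, and it errs upward.

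A reader might also infer heavy loss of patients through missing items. With 0.25–1% missing per item, independently, 1 − 0.9975³⁵ = 8% to 1 − 0.99³⁵ = 30% would lack at least one. That needs independent omissions and complete-case deletion, neither of which the protocol states. Section 8.2.3 and Annex 3 also tell staff to check the forms and have omissions completed. I put no weight on that range.

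A third inference is an inflated type I error from pooling variances. The 6.3% needs the experimental group to be less variable, the reverse of what the sample-size section raises. In the direction it raises, pooling is conservative.

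Finally, *items* may be loose wording for dimension scores; the EQ-5D covariates are unstated rather than excluded; and detail is left to an analysis plan not at hand. All of that is fair and makes this a moderate point. It does not remove it: the one covariate list given for the quality-of-life comparison names neither the baseline of the score analysed nor centre.

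**Conclusion.** The point holds as one of efficiency and mild conservatism. As written, the covariate list risks a standard error about 5% larger than necessary for MOS-HIV, if items means the 35 responses. For EQ-5D VAS it forgoes up to 13–29% of residual SD, less what MOS-HIV baselines or analysis of change recover. Leaving out centre makes the model standard error roughly 1–7% too large, less under imperfect balance and not at all if centre does not predict outcome. The correlations, ICC and number of centres are assumptions, not protocol figures. No false-positive inflation is shown in the direction that the protocol anticipates. The change is worth making because it is nearly free and the unadjusted design has only 80.2% power; the trial's validity does not depend on it.

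**What to change.** Reword section 12.4 so that, for each primary outcome, the week-24 score (or its change from baseline) is analysed by ANCOVA on arm, the baseline value of that same score, centre, age and sex. State whether the MOS-HIV covariate is a total or a dimension score, and name baseline EQ-5D VAS for the EQ-5D VAS model. Small centres can be pooled by a rule fixed in advance, or centre fitted as a random effect. Heteroscedasticity-robust standard errors can be added as an optional sensitivity analysis, given the unequal variability that the sample-size section mentions.

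The cost is a few lines of text and the rule for small centres. Every variable is already collected, and the sample size of 372 evaluable patients remains adequate.
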